### Blinding

The researchers taking measurements for either primary or secondary outcome measures, as described herein, will be blind to the group assignment. On completion of the study, volunteers will be asked to which group they believe they were assigned, to allow assessment of the blinding success [25].

The nutritionist, who delivers the diets, the only non-blinded intervention, will not be aware of the pills supplied to the unmodified diet groups and will not be involved in other steps of the protocol. The scoring of the apnea-hypopnea index will be performed remotely via the internet by a third-party certified scorer. The blinding code will be broken at the end of the study or earlier by request of regulatory committees or in the case of adverse events in connection with the group assignment.

### Recruitment

A list of patients who recently underwent polysomnography at the affiliated sleep laboratory and signed a form consenting to participate in research will be generated. Those patients with an apnea-hypopnea index greater than 30 events/hour will be selected and contacted by telephone. If they have no prescription by their physicians to start treatment in the next week, they will be invited to participate. The acceptors will be asked to visit the research center where the informed consent process will be conducted.

### Data management

The data will be entered in a password-protected computer system by researchers not otherwise involved in the protocol. The system performs a range check of the data values entered. A second person will make a visual check, comparing original documents with entered data to correct discrepancies. The database is backed up each 15 minutes in a computer located remotely at the university and in an international data safety company.

### Statistical methods

Outcomes will be analyzed by intention-to-treat and per-protocol. A low attrition rate is expected, since the interventions are of short duration and minimal risk. Missing data will be considered as missing. Data imputation will not be employed.

Normally distributed data will be presented as means and standard deviation. Non-normally distributed data will be displayed as median and interquartile range. Natural logarithm transformation of the apnea-hypopnea index in events/h will be employed to correct its non-normal distribution in analyses that assume normal data distribution. The significance of the differences between intervention groups will be tested by chi-squared test for categorical variables and generalized estimating equations method, followed by pairwise comparisons with the sequential Bonferroni correction for continuous variables. Logistic and linear regression models will be used to adjust results for age and body mass index. Results with a *P* value lower than 0.05 for alpha error will be considered statistically significant. Statistical analyses will be performed using SPSS software (SPSS Inc., Chicago, IL, USA).

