### Sample size

Sample size calculations were performed for repeated measures analysis of variance using G*Power software 3.1.9.2 [23]. Hypothesizing an effect size of 0.25 for a power of 90% at *P* alpha < 0.05, for three groups, a sample size of at least 18 in each arm of the study was required, totaling 54 individuals. In case of loss to follow-up, extra volunteers will be enrolled to compensate. Losses will be included in the intention-to-treat but not in the per-protocol analyses.

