### Follow-up and duration of the study

There will be two visits at the clinical research center, one before (baseline) and one after (follow-up) the one-week pill plus diet intervention.

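### GEE, a large-sample method, is named for 18 men per arm with no small-sample correction; with large-sample tests the 5% level would become roughly 5.5 to 7.7%

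*Protocol article*

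**What the plan says.** Under Statistical methods, the protocol article assigns continuous outcomes to the "generalized estimating equations method, followed by pairwise comparisons with the sequential Bonferroni correction for continuous variables". The primary outcome, the apnea-hypopnea index, is one of them and is log-transformed where normality is assumed. A P "value lower than 0.05 for alpha error will be considered statistically significant". The section also names linear regression, for adjustment by age and body mass index.

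Under Sample size, a different method is used: "Sample size calculations were performed for repeated measures analysis of variance using G*Power software 3.1.9.2". The inputs are three groups, alpha 0.05 and "Hypothesizing an effect size of 0.25 for a power of 90" per cent, and the result is that "a sample size of at least 18 in each arm of the study was required, totaling 54 individuals". Follow-up and duration of the study gives two visits per man, baseline and one week later.

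The article does not state the GEE variance estimator (robust or model-based), the test statistic, its reference distribution or the working correlation.

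**The concern.** In a GEE analysis each man is one cluster, so there are 54 clusters, 18 per arm. Two large-sample shortcuts matter at that size:

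- The uncorrected robust sandwich divides each arm's sum of squares by n where n − 1 is needed, so the standard error is slightly too small.
- Wald chi-square and z tests treat the estimated variance as known. The F and t tests of the ANOVA used for sizing do not.

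Both push rejection rates above the nominal level. The effect falls on the primary outcome of a proof-of-concept trial, whose Discussion says that a positive result would lead to further, larger trials. A false positive is therefore costly.

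**Working it through.** **1. Reproduce the stated sample size.** The inputs are k = 3 groups, m = 2 visits, f = 0.25 (read as Cohen's f) and alpha 0.05. The correlation between visits is not stated; ρ = 0.5 is assumed. For the group-by-time interaction:

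λ = f²·N·m/(1 − ρ) = 0.0625 × 54 × 2/0.5 = 13.5, with (k−1)(m−1) = 2 and (N−k)(m−1) = 51 df.

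Power is 0.9016, so 54 is reproduced. With ρ of 0, 0.3 or 0.7 the same formula gives 105, 75 or 36. The stated size thus fits an F test of the interaction at ρ = 0.5.

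**2. What GEE reduces to here.** With a group-by-time model, two visits and complete data, each treatment contrast is a difference between arms in mean change. The uncorrected sandwich variance of one arm's mean change is SS/n², where the unbiased form is SS/[n(n − 1)]. The ratio of standard errors is √(17/18) = 0.972, or 2.8% too small.

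**3. One pairwise test, exact under normality.** With equal arms, the robust Wald z equals the two-sample t (34 df) times √(18/17).

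- At 0.05: |z| > 1.960 means |t| > 1.960 × 0.972 = 1.905, and P(|t₃₄| > 1.905) = 6.5%.
- At the first sequential Bonferroni step, 0.05/3 = 0.0167: |z| > 2.394 means |t| > 2.327, with probability 2.6%. That is 1.57 times nominal. The excess is larger as a ratio than at 0.05, but smaller in points (about 1.0 against 1.5).

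**4. Simulation under the null.** 200,000 trials, 18 per arm, normal changes, equal variances, complete data, nominal 5%:

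| Variance and reference | Omnibus | One pair | Sequential Bonferroni, 3 pairs |
|---|---|---|---|
| Uncorrected sandwich, chi-square/z | 7.7% | 6.6% | 6.8% |
| n − 1 sandwich, chi-square/z | 6.7% | 5.9% | 5.8% |
| Model-based, maximum-likelihood scale, chi-square/z | 6.9% | 6.3% | 6.2% |
| Model-based, N − p scale, chi-square/z | 6.0% | 5.6% | 5.3% |
| Leverage-corrected (Mancl-DeRouen type) sandwich, F | 4.9% | – | – |
| n − 1 variance, t | – | 5.05% | 4.4% |
| Pooled variance, F/t | 5.0% | 5.1% | 4.4% |

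A rerun with 1,000,000 trials gave 7.7%, 6.5% and 6.7% for the first row. The pairwise value matches the exact result in step 3, and these are the figures used in the conclusion.

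**5. Sensitivity of the first row.**

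- Skewed data: 7.5%, 6.6%, 6.6%. Heavy-tailed data (t with 5 df): 7.3%, 6.4%, 6.3%.
- 16 men per arm: 8.1%, 6.8%, 7.1%.
- Two comparisons with control only, sequential Bonferroni: 6.7%.
- Pairwise tests counted only after a significant omnibus test: family-wise 6.0 to 6.6%.
- 3,000 full GEE fits (exchangeable, ρ = 0.5): omnibus 7.4%, pairwise 6.6%. Model-based variance in the same fits: 6.8% and 6.2%.
- 100 men per arm: omnibus 5.2%, pairwise 5.1%. The excess is a small-sample effect.

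**6. Where the excess comes from.** For the omnibus test the excess is 7.7 − 5.0 = 2.7 points. Correcting the standard error alone brings 7.7% to 6.7%, that is 1.0 of 2.7 points, or 37%. The remainder comes from referring the statistic to a distribution that treats the variance as known.

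**The case against.** The strongest objection is that the article does not commit to the specification that gives 6.5 to 7.7%. It names GEE and a 0.05 level, but not a robust variance, a Wald test or a chi-square reference. Filling those in from software defaults would rest on something outside the documents. A condensed article may leave such settings to an analysis plan that is not shown, and a corrected GEE is compatible with the text. This stands: a reader might infer that the trial's true type I error is 6.5 to 8%, and the document does not support that. Choices consistent with it run from about 5% to 7.7%, and 8% is passed only with 16 per arm, whereas the article plans at least 18 and replaces losses.

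Three further inferences also go too far:

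- That small standard errors are the main cause. They account for less than half.
- That reported confidence intervals will be too narrow. The article mentions no confidence intervals.
- That sizing by ANOVA and analysing by GEE makes the sample size wrong. The figure of 54 is reproduced under ρ = 0.5, no loss of power was shown, and the pairing is a common approximation.

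What the objection does not remove is that the article fixes a large-sample method for 18 men per arm. In the base case, every version with chi-square or z tests and no small-sample correction to the variance exceeds 5%. A method in line with the sizing calculation would not.

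**Conclusion.** The point holds in conditional form and is modest in size. For an uncorrected sandwich with Wald tests, the excess over 5% is about 1.5 points for one pairwise test, 1.7 for the sequential Bonferroni family and 2.7 for the omnibus test. For a model-based variance with large-sample tests, pairwise and omnibus error is about 5.5 to 6.9%. These figures assume equal variances, complete data, roughly normal changes on the log scale and two-sided tests (the article does not state sidedness). Skewed or heavy-tailed data change them little.

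It is worth acting on because it concerns the primary outcome and because a t/F-based method is easier to defend at this size. It does not call the design or the sample size into question.

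**What to change.** Analyse the log apnea-hypopnea index and the other continuous outcomes with one of the following, fixed before unblinding:

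- **Preferred:** a linear model of the follow-up value adjusted for baseline (ANCOVA), or a linear mixed model over the two visits with Satterthwaite or Kenward-Roger degrees of freedom. Use an F test for the three-arm comparison and t tests for the pairwise ones, keeping the sequential Bonferroni step. This agrees with the F test used for sizing, and linear regression is already among the named methods.
- **If GEE is kept:** name the variance estimator and the reference distribution together. Correcting only one is not enough: the n − 1 sandwich with chi-square still gives 6.7% for the omnibus test, and the uncorrected sandwich with F also gives 6.7%. A leverage-corrected sandwich with an F reference gave 4.9%.

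The cost is a change of analysis wording and slightly wider intervals. For a pairwise difference at 0.05, the multiplier goes from 1.905 (step 3 of the working) to the t critical value of 2.008 on 51 df, and 2.008/1.905 = 1.054, so about 5% wider. No extra patients or measurements are needed.

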**Methods/design:**

This is a randomized clinical trial including men with an apnea-hypopnea index greater than 30 events/hour, previously diagnosed by full-night in-laboratory polysomnography. A total of 54 men will be included and randomly assigned to three groups: Diuretic (*n* = 18), sodium-restricted diet (*n* = 18), and control (*n* = 18). The intervention will last one week. Intention-to-treat and per-protocol analyses will be performed. The diuretic group will receive combined spironolactone 100 mg plus furosemide 20 mg daily, taken in the morning. The diet group will receive a regimen with a maximum intake of 3 g of sodium per day. The control group will receive a placebo pill and will maintain all eating habits while keeping a recall diary of their dietary behavior. The primary outcome measure will be change in apnea-hypopnea index. The secondary outcome measures will be variations of: anthropometric and bioelectrical impedance variables, office blood pressure, respiratory variables from in-home level III polysomnography, excessive daytime sleepiness, glycolipid profile, C-reactive protein, 24 h urinary variables, and adverse events.

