### Research question

Is a diuretic or a sodium-restricted diet capable of reducing the apnea-hypopnea index in comparison with a control group?

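### The pairwise correction covers three comparisons although the research question asks for two, which costs a modest amount of power for the comparisons with control

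*Protocol article*

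**What the plan says.** The Research question section poses one question with two contrasts: "Is a diuretic or a sodium-restricted diet capable of reducing the apnea-hypopnea index in comparison with a control group". No objective or hypothesis in the article asks whether the diuretic and the diet differ from each other.

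The Statistical methods section sets the analysis of continuous outcomes in two stages. The first is an overall test: "The significance of the differences between intervention groups will be tested by chi-squared test for categorical variables and generalized estimating equations method". The second is "followed by pairwise comparisons with the sequential Bonferroni correction for continuous variables". The pairs are not restricted to those involving the control arm. The threshold is a P "value lower than 0.05 for alpha error will be considered statistically significant"; whether tests are one-sided or two-sided is not stated.

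The Sample size section rests on a different test: "Sample size calculations were performed for repeated measures analysis of variance using G*Power software 3.1.9.2". Its result is that "for three groups, a sample size of at least 18 in each arm of the study was required, totaling 54 individuals". The pairwise stage does not enter that calculation.

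**The concern.** A sequential Bonferroni (Holm) procedure over k comparisons tests the smallest P value at 0.05/k, the next at 0.05/(k − 1), and so on, stopping at the first failure. Every comparison in the family makes the early steps stricter for the others. Here one of the three pairs, diuretic versus diet, answers no stated question, yet the two comparisons that do answer the research question pay for it.

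At stake is power in a trial with 18 men per arm. The answer to the research question comes from the pairwise stage, so a needlessly strict threshold there makes it more likely that a real effect of one arm, especially the weaker one, is missed.

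**Working it through.** **Inputs from the article.** Three arms, 18 per arm, N = 54; effect size f = 0.25, power 90%, alpha 0.05 (Sample size); two visits, baseline and follow-up (Follow-up and duration of the study).

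**Assumptions not in the article.** Correlation between visits rho = 0.5, sphericity, two-sided tests, and the pattern of arm means.

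**Step 1: reproduce the sample size.** For the group-by-visit interaction in a repeated measures ANOVA with m = 2 visits:

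lambda = f² × N × m / (1 − rho) = 0.0625 × 54 × 2 / 0.5 = 13.5, with 2 and 51 degrees of freedom.

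Power is 0.902, and 54 is the smallest multiple of three that reaches 90%. The other variants tried (within-subject or between-group effect, the alternative effect-size convention, rho of 0, 0.3 or 0.7) do not give 54. The stated figure therefore reproduces, but only with rho = 0.5 assumed.

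**Step 2: convert to a difference in change.** If both active arms differ from control by d (in SDs of change), the squared deviations of the three means sum to d²(1/9 + 1/9 + 4/9) = 2d²/3. Then lambda = 18 × 2d²/3 = 12d² = 13.5, so d = √1.125 = 1.06. The same d applies if only one arm works. For a graded effect with lambda = 13.5, the differences are 1.22 and 0.61 SD.

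**Step 3: first-step thresholds.** Three pairs: 0.05/3 = 0.0167. Two pairs: 0.05/2 = 0.025. Whatever the effects, Holm over three can never reject more of the two control comparisons than Holm over two.

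**Step 4: power of the whole procedure.** Simulation of 200,000 trials per scenario on change scores, 18 per arm, pooled SD with 51 degrees of freedom:

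| Scenario | Target | Holm over 3 | Holm over 2 |
|---|---|---|---|
| Both arms, 1.06 SD | each control comparison | 0.79 | 0.85 |
| | both shown | 0.70 | 0.79 |
| | at least one | 0.88 | 0.91 |
| One arm, 1.06 SD | its comparison | 0.79 | 0.81 |
| Graded, 1.22 / 0.61 SD | stronger arm | 0.88 | 0.91 |
| | weaker arm | 0.35 | 0.43 |
| Both arms, 0.8 SD | each control comparison | 0.50 to 0.51 | 0.59 to 0.60 |
| | at least one | 0.64 | 0.70 |

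**Step 5: require a significant overall test first.** Gains shrink slightly. Both arms at 1.06 SD: 0.79 to 0.84 per comparison, and 0.88 to 0.90 for at least one. One arm: 0.79 to 0.80. Graded: weaker arm 0.35 to 0.43, at least one 0.885 to 0.895.

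**Step 6: error rate.** With no effect in any arm, the chance of at least one false rejection among the two control comparisons is 0.032 with Holm over three and 0.046 with Holm over two. Both are below 0.05.

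**Step 7: range over rho.** With f = 0.25 held, d = √(6.75 / [12(1 − rho)]). First-step power by normal approximation is Φ(d√(18/2) − z) = Φ(3d − z), with z = 2.394 at 0.0167 and 2.241 at 0.025:

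| rho | d | at 0.0167 | at 0.025 |
|---|---|---|---|
| 0.3 | 0.90 | 0.616 | 0.673 |
| 0.5 | 1.06 | 0.785 | 0.827 |
| 0.7 | 1.37 | 0.957 | 0.969 |

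The first-step difference is about 6, 4 and 1 points. Its direction does not change.

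**The case against.** Testing every pair after an overall test is an ordinary choice in a three-arm trial. It fits a Statistical methods section that speaks of differences between groups and a sample size built on a three-group ANOVA. Error is controlled. The research question is phrased with an or, and for showing at least one effect the gain at the planned effect is only about 1 to 3 points. The article never says that all pairs are tested, and the confirmatory family could be defined in an analysis plan that is not shown.

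Most of this stands, and it limits the point to efficiency. It does not remove it: the article does fix a correction rule, the plain reading of unrestricted pairs among three arms is three, and one of them is not asked for.

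Three stronger readings are tempting and not supported:

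- A reader might infer that the pairwise table would be run on the six group-by-visit means, giving a far larger family and replacing between-arm tests by before-after tests. The article describes no such table; its stated target is differences between intervention groups.
- A reader might blame the third pair for the whole gap between 90% and the pairwise power. Much of that gap arises because 90% refers to the overall test. Even with two comparisons, power is 0.81 to 0.85 when one or both arms work at 1.06 SD.
- A reader might use the point to argue for another estimator, such as baseline-adjusted follow-up values. Nothing about the number of comparisons supports that.

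**Conclusion.** The point holds as a modest loss of efficiency. The correction covers a comparison that the research question does not ask for. At the planned effect this costs about 2 to 8 points of power per comparison with control, and about 9 points for showing both arms effective. At 0.8 SD in both arms the cost per comparison is about 9 points.

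The direction is certain on the plain reading of three pairs. The sizes rest on rho = 0.5, on differences back-calculated from f = 0.25 and N = 54, on two-sided tests and on the assumed patterns of means, none of which the article states. The results of the trial would be valid if the plan were left as it is.

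**What to change.** For the primary outcome, name two confirmatory contrasts in change in ln(AHI), diuretic versus control and diet versus control, and test them by the sequential Bonferroni procedure over two at an overall 0.05. Report diuretic versus diet as exploratory, with its confidence interval.

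This changes analysis wording only and needs no extra participants or visits. The price is that diuretic versus diet loses confirmatory status. If the investigators do want a confirmatory answer there, they should add it to the research question and keep three pairs.

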### Monitoring

No committee will be monitoring the data. All analyses will be performed at the end of the study.

### Study measurements

#### Description of interventions, comparison groups, and follow-up

The patients will be allocated to a combination of medication and diet intervention. A detailed description of the combinations of pill plus diet interventions is shown in Figure 1.

**Figure 1 Fig1:**
[figure not shown]
Flow diagram of the study design.

Identical pills and flasks will contain either active drug (spironolactone 100 mg plus furosemide 20 mg) or cellulose. The diet interventions will be either instruction to maintain unchanged the present alimentary habits or a diet restricting sodium intake to a maximum of three grams per day.

The inception of the one-week intervention will occur only after volunteers confirm that in this specific week they will not participate in social events, gatherings, celebrations, travels, visits to restaurants, in such way that the adhesion to the dietary instructions will be made easier.

The sodium-restricted diet will enforce the following rules: (1) Do not use salt in cooking; (2) Do not use the salt shaker; (3) To flavor foods, use spices, herbs, and other seasonings, such as olive oil, lemon, herbs, garlic, onion, parsley and chives, instead of salt; (4) Do not eat any industrialized food, such as sauces, soups, sausages, canned food, frozen, salted snacks, cheese, salami or sausages; (5) Eat fresh salads and vegetables; (6) Do not add high-sodium seasonings, such as soy sauce; (7) Eat fruit for dessert; do not eat baked desserts. The complete dietary rules will be delivered to each volunteer in a four-page handout.

### Ethics

The study was approved by the Ethics Committee of the Hospital de Clínicas de Porto Alegre under the number 130272. This committee is accredited by the Office of Human Research Protection as an Institutional Review Board (IRB0000921). The study has been registered under the number NCT01945801 at www.clinicaltrials.gov. All participants will be asked to sign the approved informed consent form prior to participation in the study.

Authorship eligibility will follow the guidelines of the International Committee of Medical Journal Editors. Professional writers will not be used. The trial results will be published in a high impact international journal. The investigators will communicate trial results to participants via email. No publication restrictions will be implemented.

#### Outcomes

*Primary outcomes*Number of apneas and hypopneas per hour of sleep (apnea-hypopnea index)

*Secondary outcomes*Adverse eventsAnthropometry (body weight and height; neck, waist, hip, ankle, and calf circumferences)Bioelectrical impedance variablesUrinary electrolytes and metabolitesOffice blood pressureRespiratory variables from the type III portable polysomnographyExcessive daytime somnolenceGlycolipid profileInflammatory marker

